### Blinding

Patients will be informed of the type of treatment that they will receive. The therapists will know the allocation so they should learn how to communicate with patients to ensure treatment blinding. In order to reduce the risk of bias, evaluators, data managers, and statisticians will be unaware of the group assignments in the result evaluation procedures and data analysis. The blinding procedure will be operated until the data are locked.

### Interventions

The Tuina protocol used in this trial is the same as those used in our previous studies [38, 39]. It includes soft tissue manipulation and spinal manipulation, such as rolling, pressing, and tapping. Yijinjng for NCNP patients was designed on the basis of the textbook which has been used for teaching students in the universities of TCM [40, 41].

Participants in the Tuina group or the Yijinjng combined with Tuina group will receive Tuina treatment 3 times a week for 8 weeks. The treatment room will be controlled at 23–25° to ensure that the participants feel comfortable. The participants will be asked to rest for 15 min before Tuina treatment. They will be advised to lie in the prone position during the treatment. The intensity level of Tuina is based on physical examination and the therapist’s clinical experience, as well as after careful communication with each study participant. Tuina treatment will last for 25 min.

The participants who are in the Yijinjng combined with Tuina group will practice Yijinjing 3 times a week for 8 weeks. The patients will be assembled once a week for practicing Yijinjing together. The Yijinjing teacher will teach them how to practice Yijinjing. The teacher will also correct the wrong movement of patients. The patients will practice Yijnjing another two times per week at home. A digital video disk about the movements of Yijinjing in this trial will be provided to the participants. They can review the movements at home easily. The participants are asked to film themselves and sent it to the teacher by email or WeChat. The teacher will examine the participants’ video carefully and give the patients some advice about practicing Yijinjing. Yijinjing treatment will last for 30 min.

VAS, NDI, SAS, soft tissue hardness, and AROM will be assessed at the baseline and 4, 8, and 12 weeks.

### Tuina group

In this arm of study, the Tuina therapist will administer a three-step protocol intended to alleviate neck pain and restore neck function by relaxing the soft tissue of the neck and shoulder. The specific protocol used is described below.

#### Step 1: Soft tissue manipulation

Patients are instructed by the therapist to lie in the prone position and to relax their mind and body naturally. Non-specific chronic neck pain conditions will be carefully examined by postural and palpatory assessment prior to treatment. The therapist will relax soft tissue and stiff muscles of the neck and shoulder by pressing-kneading manipulation for 5 min. Then, the therapist will use his palms to roll the trapezius muscle gently so as to relax the back area for 5 min. The aim of this step is to resolve adhesion and increase general circulation.

#### Step 2: Clicking on the acupuncture point manipulation

The therapist will press and knead GB20, DU16, GB21, SJ14, and SI14 for 2 min each. This step is performed to unblock Qi stagnation and remove blood stasis by separating adherent fascicles. The amount of force used is determined by the patient’s Deqi sensation, often described as a dull pain, heaviness, numbness, or soreness, and it is commonly regarded as an indicator of manipulation effectiveness in acupuncture and Tuina [42, 43].

#### Step 3: Spinal manipulation

The spinal manipulation will be used after the above two steps have relieved the tensions of the muscles and soft tissues. The patient will be instructed to sit in an orthopnea position in order to ensure the safety of manipulation. First, the therapist can exert a gentle torque to align the patient’s neck area and use the shake method to relax this area. Then, the therapist will press one thumb on the deviated spinous process while another palm holds the lower jaw. Using gentle tractions and twisting of the neck, the therapist should hold this position for a moment and then made an abrupt pulling motion to advance the stretch by 5 to 10°.

### Yijinjing combined with Tuina group

In this arm of study, the steps of Tuina treatment are the same as the Tuina group. The Yijinjing teacher will administer a five-step protocol intended to improve the therapeutic effects and adjust physical and mental conditions. The main movements of Yijinjing are shown in Fig. 2.

**Fig. 2 Fig2:**
[figure not shown]
The main movements of Yinjining. The picture is from the “Teaching video of Yinjining for NCNP patients” self-recorded by the research group. The teacher in the video is [name], a member of the research group. **A** The third aspect of Wei-tuo. **B** Taking away a star and changing the Dipper for it. **C** Nine demons drawing their swords. **D** Bowing and salutation. **E** Wigging the tail

#### Step 1: The third aspect of Wei-tuo

Take a step to the left, raise the hands in front of the chest with palms up, fingertip facing. Rotate the wrists and raise the palms above the head. Slightly bend the elbow, look upward towards the dorsum of the palm. Lift the heels, stand on toes. Hold for 5 s. Then, make fists, rotate the wrists, and put the fists down to the waist slowly. Place the whole feet on the ground. Repeat the whole procedure 3 times in 6 min.

#### Step 2: Taking away a star and changing the Dipper for it

Move the right foot to the right front. Raise and straighten the right hand, direct the palms facing downward, slightly turn the head to the right side, and fix the eyes on the right palm. Bend the left elbow and put it naturally on the back of the body. Hold for 5 s. Then, put the hands to both sides of the body and relax when exhaling. Exchange the left side for exercising. Repeat the whole procedure 3 times in 6 min.

#### Step 3: Nine demons drawing their swords

Take a step to the left. Cross the hands over the chest and raise up. Separate the hands above the head. Put the left hand on the neck and the right hand to the back. Raise the head to the left 45° and twist waist. Pull the hands tightly when exhaling. Hold for 5 s. Then, put the hands to both sides of the body and relax when exhaling. Exchange to the right side for exercising. Repeat the whole procedure 3 times in 6 min.

#### Step 4: Bowing in salutation

Separate the legs and hold the head by the hands. Bend the waist between the knees. Stretch the head between the legs. Use finger to tap the head 7 times. Then, straighten the knee and waist when exhaling and stand upright. Repeat the whole procedure 3 times in 6 min.

#### Step 5: Wagging the tail

Take a step to the left. Cross the hands in front of the chest and raise the hands above the head. Fix the eyes to the hands. Then, bend the upper body upward and press down your hands to the ground. Raise up the head and open the eyes. Bend the body and place the heels when exhaling. Strengthen the body and lift the heels when inhaling. Repeat the whole procedure 3 times in 6 min. The patient can adjust the degree of flexion and extension according to his own physical condition.

### Study therapists

Tuina will be performed by a senior therapist who has studied Tuina and has held a practitioner’s license for more than 10 years. He/she must have received professional training in Tuina. Yijinjing will be conducted by a Yijinjing teacher with 10 years of teaching experience. Both Tuina therapist and Yijinjing teacher will be trained for a week. They must pass a test to ensure consistency of the study methods before participating in the trial.

### Allowance of concurrent treatment of patients

All other treatments for NCNP will be banned during the trial, including drug of non-drug. They may receive treatment which is not related to neck pain. Any change of concurrent treatments will be recorded.

### Outcome measurements

The efficacy between the two groups will be assessed by primary outcome measure: change in visual analog scale (VAS) four times (week 0, week 4, week 8, and week 12) (Table 1). The secondary outcomes measured at these four time points included (1) Neck Disability Index (NDI), (2) Self-Rating Anxiety Scale (SAS), (3) a digital pressure algometer used to assess tissue hardness, and (4) SH-105 used to assess cervical AROM (active range of motion).

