### Specific primary objective

The specific primary objective is to determine the change in the visual analog scale (VAS) pain scores from baseline, 4 weeks during the intervention, at the end of the intervention, and 1 month after the intervention within and between the two groups.

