### Sample size calculation

The following two hypotheses are related to the differences between the two groups.
H0:μ1 − μ2 ≤ ΔH1:μ1 − μ2 > Δ

where μ1 is the VAS score for treating 8 weeks in the Tuina group, and μ2 is the VAS score for treating 8 weeks in the Tuina combined with Yijinjing group.

According to a previous clinical study in China [53], the mean and standard deviation of VAS in the Tuina group (*n* = 34) after the intervention was 5.5 and 1.1, respectively. The mean and standard deviation of VAS in the Tuina combined with neck exercise group (*n* = 34) after the intervention was 4.7 and 1.3, respectively.

The following formula was used to calculate the sample size in this trial:
$$ n=\frac{2{\left({z}_{\alpha /2}+{z}_{\beta}\right)}^2\times \kern0.5em {\sigma}^2}{{\left({\mu}_2-{\mu}_1-\varDelta \right)}^2} $$

$$ {\displaystyle \begin{array}{l}n=\frac{2{\left(1.96+0.84\right)}^2\times {1.3}^2}{{\left(4.7-5.5-0\right)}^2}=42\\ {}\end{array}} $$

(*α* = 0.05 *β* = 0.2, superiority design, the two-sided test, *Δ* = 0)

Considering a dropout rate of 20%, each group will require 51 cases. Therefore, a total of 102 participants should be recruited for this randomized controlled trial (RCT).

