### Statistical analysis

All statistical analyses will be performed with the SPSS software (SPSS, version 24.0, SPSS Inc., Chicago, IL, USA) by statisticians who are independent of the research team and blinded to the group allocation. Data analysis will be based on the intention-to-treat (ITT) principles. The statistical significance was accepted for values of *p* < 0.05. Participants who fail to complete the study will be treated as having no change from baseline at all times. Descriptive statistics will be used to compare demographic and baseline information and evaluate the credibility of the groups. The normality of data will be tested by the Kolmogorov-Smirnov test. Parametric statistics (Tukey test) or non-parametric statistics (Wilcoxon rank sum test) will be used for the within- and between-group according to the results of homogeneity and normality analysis. If the data does not conform to a normal distribution, a covariance analysis will be used. The efficacy will be measured at four time points. A repeated measures analysis of variance will be conducted to analyze dependent variables (from baseline and follow-up). The Bonferroni and Dunn tests will be used for multiple comparisons. The intra-group comparison (comparison between baseline and follow-up) will be tested by a two-sided paired *t* test. The difference of categorical variables (VAS, NDI, SAS, PPT, AROM) and adverse effects between the groups will be analyzed by using The chi-square test or Fisher’s exact test. All numerical data will be presented as the mean ± SD, and categorical variables will be described with percentages (%). If it is necessary, post hoc analyses will be performed. The confidence interval will be established at 95% and the significance level at 0.05.

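### The primary VAS outcome spans three post-baseline visits and includes within-group change, but the sample size is for one between-group comparison at week 8, and no deciding test is named

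*Protocol article*

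**What the plan says.** Four sections of the protocol article bear on the primary analysis.

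- **Outcome measurements** introduces a between-group assessment of efficacy by the "primary outcome measure: change in visual analog scale (VAS) four times (week 0, week 4, week 8, and week 12"). Week 0 is baseline, so there are three post-baseline visits. None is singled out.
- **Specific primary objective** covers "the change in the visual analog scale (VAS) pain scores from baseline, 4 weeks during the intervention, at the end of the intervention", and then "1 month after the intervention within and between the two groups". It is the only one of the four to put within-group change into the primary question.
- **Sample size calculation** sets H0 and H1 on a single difference. It says that "μ1 is the VAS score for treating 8 weeks in the Tuina group" and defines μ2 likewise for the combined group. The stated basis is alpha 0.05, beta 0.2 and "superiority design, the two-sided test", with Δ = 0.
- **Statistical analysis** accepts p < 0.05 and says "A repeated measures analysis of variance will be conducted to analyze dependent variables (from baseline and follow-up"). It also lists parametric or rank tests within and between groups and paired t tests within groups, and names Bonferroni and Dunn tests for multiple comparisons. It does not define the family they cover or name the result that decides the trial.

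**The concern.** A confirmatory trial needs one stated comparison on which its claim rests, or a stated rule for combining several. Here the sample size section implies one (between groups, week 8), while the objective and outcome sections describe at least three between-group comparisons plus within-group ones. The analysis section does not resolve the difference.

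Two things are at stake. If any visit may carry the claim without correction, the false-positive rate exceeds 5%. If the named correction is spread over the visits, the week-8 comparison no longer has the power that justified the sample size. In either case the choice of visit and test stays open until data are seen.

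The within-group element is a separate weakness. Both arms enter at VAS ≥ 3 and both receive Tuina three times a week for 8 weeks. Improvement from baseline is therefore expected in each arm through regression to the mean and through Tuina itself. A significant paired test says nothing about what Yijinjing adds.

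**Working it through.** **Inputs from the document (Sample size calculation).** Means 5.5 and 4.7, so the difference is 0.8 cm; SD used 1.3; two-sided alpha 0.05; power 80%. **Assumed, because the document gives no value:** the correlation between visits (ρ), and the group differences at weeks 4 and 12.

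**1. The plan's own figure.** n = 2(1.96 + 0.84)² × 1.3² / 0.8² = 41.4, so 42 per group. This is reproduced. The standardised effect at n = 42 is 0.8 / (1.3 × √(2/42)) = 2.820, and power is Φ(2.820 − 1.960) = 80.5%. This holds for one week-8 comparison at the full 5%.

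**2. Three uncorrected between-group tests, any one counting as success.** If independent, 1 − 0.95³ = 14.3%. Simulation of three equally correlated normal statistics (2,000,000 draws) gives:

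| Assumed ρ | 0 | 0.3 | 0.5 | 0.7 | 0.9 |
|---|---|---|---|---|---|
| Family-wise error | 14.3% | 13.6% | 12.5% | 10.9% | 8.4% |

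**3. Bonferroni over three visits (0.05/3 = 0.0167 each, critical value 2.394).** Unadjusted week-8 power with 42 per group is Φ(2.820 − 2.394) = 66.5% (64.7% by noncentral t). Restoring 80% takes 56 evaluable per group, or 56/0.8 = 70 recruited per group (140 in total) at 20% dropout.

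**4. The same with baseline adjustment.** The residual SD is 1.3√(1 − ρ²). Week-8 power with 42 per group by noncentral t:

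| Assumed ρ | 0.3 | 0.5 | 0.7 |
|---|---|---|---|
| Single test at 5% | 83% | 90% | 97% |
| Bonferroni over three visits | 69% | 79% | 93% |

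The rows of this table can be compared with each other. Setting the unadjusted 66.5% against the adjusted single test would mix the gain from the covariate with the cost of multiplicity.

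**5. Repeated-measures ANOVA.** This is not the test that was sized, and its power depends on which effect is tested. Take illustrative differences of 0/0.4/0.8/0.6 cm at weeks 0/4/8/12, SD 1.3, n = 42 and compound symmetry.

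- Group main effect with baseline as a repeated level: mean difference 0.45 cm, variance 1.69(1 + 3ρ)/4. Baseline, where the expected difference is zero, dilutes the effect.
- Group-by-time: noncentrality (42/2) × 0.35 / [1.69(1 − ρ)], where 0.35 is the sum of squared deviations of the four differences from 0.45; F on 3 and 246 degrees of freedom.

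| Assumed ρ | 0.3 | 0.5 | 0.7 |
|---|---|---|---|
| Group main effect including baseline | 62% | 51% | 43% |
| Group-by-time | 53% | 69% | 90% |

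The two effects move in opposite directions as ρ rises, so the ANOVA has no single power until its deciding effect is named.

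**The case against.** The week-8 intent is visible. The only formal hypotheses are between-group at 8 weeks, and the outcome section also speaks of efficacy between the groups. This stands. It makes the repair small, but the objective and outcome sections still do not carry week 8 forward.

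Inflation is not established. The analysis section names Bonferroni and Dunn, and a single omnibus ANOVA test would hold 5%. This also stands, so the 8% to 14% is conditional on uncorrected testing. But the correction has no defined family, the omnibus test is not made decisive, and the sample size was not computed for it.

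Power need not suffer everywhere. With Bonferroni and an equal effect at all three visits, the chance of winning at some visit is 96% to 76% for ρ from 0 to 0.9. That is correct, but it is not the week-8 comparison that was sized.

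A reader might infer two stronger claims that the document does not support. The first is that the trial could be declared positive on a within-group p-value. The primary objective includes within-group change and the analysis section lists paired tests, but nothing makes them a success criterion. The second is that the ANOVA necessarily forfeits the stated 80% power. Under the illustrative profile, group-by-time reaches 90% at ρ = 0.7. The wording about baseline and follow-up is also ambiguous: it may mean baseline is a repeated level, or that changes from baseline are analysed.

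A missing analysis plan does not answer the point. The primary outcome and objective are stated here, and they disagree with the hypotheses stated here.

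**Conclusion.** The mismatch is in the text and should be corrected. The primary outcome and objective span weeks 4, 8 and 12, and the objective adds within-group change; the hypotheses and sample size concern one between-group comparison at week 8; no test is named as decisive.

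The consequence takes one of two forms, depending on how the plan is read. Uncorrected testing at any visit gives a family-wise error of about 8% to 14% (ρ 0.9 to 0). Bonferroni over three visits lowers week-8 power with 42 per group from 80.5% to about 66% unadjusted, or gives about 69%/79%/93% with baseline adjustment at ρ = 0.3/0.5/0.7. The ρ values are assumptions throughout. The ANOVA figures also rest on an assumed profile of differences, and show only that its power is undetermined as the plan stands.

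Within-group change does not belong in the primary objective, although the plan does not make it a criterion for success.

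**What to change.** In Specific primary objective, Outcome measurements and Statistical analysis, name one primary analysis: the between-group difference in VAS at week 8, adjusted for baseline VAS, two-sided 5%. This agrees with the hypotheses in Sample size calculation. It also settles whether the outcome is the score or the change, since with baseline as a covariate both give the same treatment contrast.

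Make weeks 4 and 12 secondary. Use baseline as a covariate and not as a repeated response. Remove the within-group comparison from the primary objective and report within-group change descriptively. If Bonferroni is kept, state which secondary comparisons it covers.

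The cost is wording in three sections, agreed before the blind is lifted. No extra patients or data are needed: 42 evaluable per group gives 80.5% power unadjusted, and 83% to 97% adjusted over ρ = 0.3 to 0.7. The small downside is that weeks 4 and 12 lose confirmatory status.

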**Table 1 Tab1:**
[figure not shown]
All measurements and measuring time points

### Primary outcome measurement

#### VAS

The intensity of NCNP will be measured by a scale of 10-cm horizontal line visual analog scale (VAS) [44]. The patients will be asked “How much pain do you have this moment?”, then the patient will mark on the 10-cm horizontal line visual analog scale. Zero means “absence of pain,” while 10 represent “the worst pain.” VAS has been proved as a valid and reliable outcome measure for recording pain with ICC = 0.96 to 0.98 according to a previous study [45].

### Secondary outcome measurements

#### NDI

The Neck Disability Index (NDI) will be used to measure the patients’ limitations in everyday life activities because of neck function [46]. It is most commonly used as a self-reported questionnaire in neck pain. It contains 10 questions, each of which comprises 6 potential answers ranging from 0 (no disability) to 5 (full disability), and the total of the NDI score varies between 0 and 50 points. The total NDI scores less than 4 indicate no disability; 5–14, mild disability; 15–24, moderate disability; 25–34, severe disability; and more than 35 points “complete disability.”

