#### SAS

The anxiety level of NCNP patients will be measured by Zung Self-Rating Anxiety Scale (SAS) [47]. Twenty questions are divided into 4 groups: cognitive, autonomic, motor, and central nervous system symptoms. Each section is scored on four levels of anxiety intensity from “1” not at all to “4” very much and with a sum score between 20 and 80. A higher total score indicates a more severe anxiety level. The total raw scores range from 20 to 80. The raw score consequently needs to be converted to an “Anxiety Index.” The primary scores should be interpreted into the Anxiety Index. The clinical interpretation of one’s level of anxiety is as follows: 20–44, normal range; 45–59, mild to moderate; 60–74, marked to severe lever; and 75–80 extreme anxiety level.

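### NDI and SAS are called categorical and sent to a chi-square or Fisher test, against the score-based analyses planned beside it, and the only categories given for them are defective

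*Protocol article*

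**What the plan says.** In the protocol article, Statistical analysis, one sentence reads: "The difference of categorical variables (VAS, NDI, SAS, PPT, AROM) and adverse effects between the groups will be analyzed by using The chi-square test", with Fisher's exact test as the alternative. The same section also plans a repeated measures ANOVA of the dependent variables over the four time points, parametric or rank tests within and between groups, paired t tests within groups, and mean ± SD for numerical data. The Specific secondary objectives are framed as change in scores.

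The NDI section builds the scale from ten items, each scored 0 to 5, and gives the resulting range: "the total of the NDI score varies between 0 and 50 points". The lowest class is set by this wording: "The total NDI scores less than 4 indicate no disability". Three middle classes follow, at 5–14, 15–24 and 25–34, and a top class takes totals above 35.

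The SAS section says: "The total raw scores range from 20 to 80". It requires conversion: "The primary scores should be interpreted into the Anxiety Index". It then lists four bands: 20–44, 45–59, 60–74 and 75–80. It gives neither a conversion formula nor a range for the index.

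**The concern.** NDI and SAS are sums of item scores. Calling them categorical and naming a contingency-table test for the group difference sets up a second between-group comparison beside the score-based ones, with no statement of which result counts.

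A statistician who tried to carry out that sentence would need categories, and the bands in the NDI and SAS sections are the only ones in the article. Two possible NDI totals belong to no band. For SAS, the reader cannot tell whether the bands apply to the raw total or to the index. At stake are a less sensitive test of two secondary outcomes, a few patients with no class, and SAS classes that depend on an unstated scale.

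**Working it through.** **Score ranges (reproducing the article's figures).** NDI: 10 items × 0 to 5 gives 0 to 50. SAS: 20 items × 1 to 4 gives 20 to 80. Both match.

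**NDI coverage.** Totals are whole numbers. The bands are 0–3, 5–14, 15–24, 25–34 and 36–50. Of the 51 possible totals, 49 fall in exactly one band, none in two, and two (4 and 35) in none. With the end bands written as 0–4 and 35–50, all 51 are covered once. Entry requires NDI ≥ 10 (Inclusion criteria), so a 4 can arise only after recruitment; a 35 can arise at any visit.

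**SAS coverage.** The bands 20–44, 45–59, 60–74 and 75–80 cover 20 to 80 without gap or overlap, so they fit the raw total exactly. They fit the index only if conversion leaves the range unchanged. No factor is given, so the following multipliers are assumptions (index rounded down):
- 1.0: nothing changes.
- 1.1: 45/1.1 = 40.9, so raw 41–44 leaves the normal band; the index reaches 88, and raw 74–80 (7 scores) lies above the top band.
- 1.25: 45/1.25 = 36, so raw 36–44 leaves the normal band; the index reaches 100, and raw 65–80 (16 scores) lies above the top band.

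The article gives no SAS distribution, so none of this converts to a number of patients.

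**Power if the NDI bands were tested.** Inputs:
- 42 per arm, from Sample size calculation: 2 × (1.96 + 0.84)² × 1.3² / 0.8² = 41.4, rounded up to 42.
- NDI mean, SD and benefit: not in the article. Assumed: Tuina mean 9 or 14, SD 4.5 or 5, and a mean 3 points lower in the combined arm.

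NDI totals were simulated as rounded normal values limited to 0–50 (2,000 trials per scenario) and compared by chi-square on the occupied bands. The t-test column is computed directly: effect size 3/4.5 = 0.67 or 3/5 = 0.60, noncentrality 0.67 × √21 = 3.06 or 0.60 × √21 = 2.75.

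| Tuina mean, SD | Chi-square, bands as written | Chi-square, bands repaired | t test on totals |
|---|---|---|---|
| 9, 4.5 | 57% | 59% | 86% |
| 9, 5 | 49% | 51% | 78% |
| 14, 4.5 | 51% | 55% | 86% |
| 14, 5 | 43% | 47% | 78% |

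Simulated t-test power ran from 76% to 87%. A repeat with 4,000 trials per scenario gave 41–57%, 46–58% and 77–86% for the three columns, so the figures are good to about three points.

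The shortfall of the bands as written is 29 to 35 points (86 − 57 = 29; 78 − 43 = 35). Repairing the bands recovers 2 to 4 of those points. The rest comes from replacing totals by bands.

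**Unclassified patients.** With m the arm mean and s the SD, the chance of a 4 or a 35 is p(m) = Φ((4.5 − m)/s) − Φ((3.5 − m)/s) + Φ((35.5 − m)/s) − Φ((34.5 − m)/s). The expected count is 42 × [p(m) + p(m − 3)], with m now the Tuina mean.

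| Tuina mean, SD | Expected of 84 |
|---|---|
| 9, 4.5 | 5.4 |
| 14, 5 | 1.7 |
| 17, 5 | 0.6 |
| 20, 5 | 0.2 |
| 20, 7 | 0.9 |
| 25, 7 | 1.4 |

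**The case against.** The strongest reply is that the bands and the test are never connected. The Statistical analysis section does not mention the bands, and its list of categorical variables includes VAS, PPT and AROM, for which the article gives no categories at all. The NDI and SAS sections present the bands as interpretation of a score. On this view the sentence is a drafting slip, and analysis as scores is already planned.

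Much of that stands. A reader might infer that patients scoring 4 or 35 will be dropped from the analysis, or that NDI and SAS will be analysed only as bands. The article supports neither: it does not tell anyone to test these bands or to exclude unbanded scores, and it plans ANOVA and parametric or rank tests as well. A reader might also blame the gaps for the power loss; repairing them hardly changes it. Nor are the SAS bands broken in themselves: they are complete, and only their scale is unclear. Finally, the rule that non-completers count as unchanged from baseline, which the calculation ignores, keeps those patients at about their entry score of 10 or more and away from 4.

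What the reply does not remove is the sentence itself. It names NDI and SAS, calls them categorical and assigns their group difference to a contingency-table test. The contradiction and the two band faults are statements in the article, not detail left to an analysis plan.

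**Conclusion.** The point holds as a minor correction to two secondary outcomes. The chi-square assignment contradicts the score-based analyses and objectives in the same article. NDI totals of 4 and 35 have no class, and the SAS bands do not say which scale they use.

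If the NDI bands were tested, power would be roughly 43–57% rather than 76–87%, almost entirely because scores become categories. The gaps affect about 0.2 to 5.4 of 84 patients over the scenarios shown (Tuina means 9 to 25, SDs 4.5 to 7). All these figures rest on assumed NDI means and SDs, a 3-point benefit and 42 per arm. They describe the chi-square comparison only, not every planned analysis of NDI. The size of the SAS problem cannot be computed from the document.

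**What to change.** In Statistical analysis, remove NDI and SAS from the chi-square sentence and compare their totals between groups with the continuous analysis already planned. VAS, PPT and AROM stand in the same sentence without any categories, so it is sensible to check them in the same edit.

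If the bands are kept for description, write the NDI end bands as 0–4 and 35 or more. State whether the SAS bands apply to the raw total or to the index, and use one scale throughout; if it is the index, give the conversion.

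The cost is wording in three sections. No new data are needed and the sample size does not change. The article reports recruitment as still open, so the wording can be settled before the data are locked.
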